## Abstract

**Background::**

Insomnia is a common disease associated with different nervous system stress response and endocrine disorders. It has been reported previously that abdominal vibration and ring massage therapy can significantly improve the symptoms of insomnia patients, enhance the activity of neurons. In addition, functional MRI (resting state brain functional magnetic resonance imaging [Rs_fMRI]) of the resting state brain test has proved that the functional connection between hypothalamus and parahippocampal gyrus could be significantly enhanced after abdominal massage treatment. It has been confirmed that there is possible involvement of brain–gut interaction effect in the treatment of insomnia, but there is a lack of research to elucidate the possible mechanisms of brain–gut interaction in the treatment of insomnia. The purpose of this study is to investigate the relationship between the hypothalamus and intestinal interaction in the treatment of insomnia by abdominal massage.

**Methods and design::**

A single blind randomized controlled trial will be conducted. Sixty chronic insomnia volunteers and 30 healthy volunteers will be recruited for this study. Sixty insomnia volunteers will be randomly divided into a drug group and a massage group, and 30 healthy volunteers will be assigned to the healthy group. The manipulation of the treatment group will be mainly carried out through abdominal rubbing and vibration massage, once a day, 30 min/time, 5 days for a course of treatment, and a total of 4 intervention courses will be carried out. Patients in the drug group will be given orally spleen-invigorating bolus, twice a day, 1 pill in the morning and 1 pill in the evening. The course of treatment will be carried for 5 days, and a total of 4 courses of treatment will be administered.

The massage group will be compared with the healthy group and the drug group by Pittsburgh Sleep Index scale (PSQI), Hyperarousal scale (HAS), Hamilton Depression scale (HAMD), Fatigue scale-14 (FS-14), and Wechsler Adult Memory scale (WAIS) scales using to observe the sleep quality. Rs-fMRI will be used to observe various BOLD signals in the brain and compare the values of Reho, fALFF, and FC. MRS technology will be used to observe the contents of GABA and 5-HT in the hypothalamus. Additionally, the contents of cortical hormone releasing hormone (CRH), adrenocorticotropic hormone (ACTH), COR, GABA, NE, PGE2, and 5-HT in the serum will be also detected. The serum of each group will be taken for 1H nuclear magnetic resonance (^1^HNMR) metabolomics study to analyze the various common metabolites, differential metabolites, potential metabolic biomarkers, and metabolic pathways among the 3 groups. Finally, in combination with the brain functional imaging and brain spectrum, the potential mechanism of abdominal vibration and ring massage will be discussed.

**Discussion::**

The results of this study will be used to possibly elaborate the various mechanisms of brain and intestine interaction in the treatment of insomnia by employing abdomen ring rubbing.

Advantages and limitations of proposed studyThe study will comprise of a safe and reliable clinical trial, which will only perform abdominal massage in patients with insomnia with almost no risk as well as high comfort level, and will thereafter investigate the possible therapeutic effects of abdominal massage on patients with insomnia.After treatment, the volunteers and patients will be assessed by PSQI, FS-14, as well as heart rate variability (HRV), and RS_fMRI, MRS, and serum metabolomics will be detected. The techniques used will be safe, harmless, and will be able to explain the potential difference between insomniacs and healthy volunteers.The basic advantages of this study will be its safety, reliability, practicability, and high comfort level. In this clinical trial, patients will be treated in a standard way, and the rights and interests of the subjects will be fully guaranteed. The limitation is the lack of double-blind control, and the drug group uses the recommended drug in the TCM guidelines.

## Introduction

1

Insomnia is the insufficient sleep time and quality and could significantly affect the subjective experience of the daytime activities. Additionally, with the rapid increase in the pace of life, as a result of significant work pressure, the incidences of insomnia, has gradually increased and patients may have trouble falling asleep and could exhibit sleep disorders, mood disorders, fatigue, irritability, causing a decrease in the work and learning efficiency. These changes can lead to serious depression, and could cause chronic heart cerebrovascular disease and neural system diseases. From the perspective of etiology, insomnia can be divided into primary insomnia and secondary insomnia, and according to the inheritance it can be divided into acute insomnia (<4 weeks) and subacute insomnia (>4 weeks and <6 months) as well as chronic insomnia (>6 months). At present, one of the major treatment options is the drug intervention to treat insomnia and the other is cognitive behavioral therapy. However, traditional Chinese medicine (TCM), complementary and alternative therapies are still not recommended in European Guideline for Diagnosis and Treatment of insomnia due to the poor quality of medical evidences to substantiate their effectiveness.^[3]^ So the investigation of potential mechanisms by which massage treatment could insomnia and the understanding of various nerve, endocrine system, and immune disorders to clarify the main direction of the pathogenesis of the insomnia is important. In the nerve—endocrine system by the hypothalamus-pituitary-adrenal axis (HPA) mediated hormonal balance. This could be of great significance in the management of insomnia.^[4]^

Abdominal vibration and ring massage therapy tradition medicine of Changbai mountain use meridians to adjust the internal organs means in the genre,^[5]^ based on the visceral massage, thereby combining modern brain–gut interaction theory. This could gradually lead to forming a “improve the brain by treating the intestines” featuring technique, safe and reliable clinical operation with obvious therapeutic impact, and no severe side effects. Moreover, bead on the results of our previous national natural fund project entitled “the abdominal massage therapy type glove 2 virtual research on the brain–gut interaction mechanism of primary insomnia (no. 81574094)” it was confirmed that the abdominal vibration and ring massage could significantly improve the symptoms of patients with insomnia, and thereby enhance neuronal activities. It could also improve the substance P in the ghrelin, neuropeptide Y, and enkephalin disorder state of matter.^[6]^ The findings of resting state brain functional magnetic resonance imaging (Rs_fMRI) test also proved that the functional connection between hypothalamus and parahippocamal gyrus was significantly enhanced after abdominal massage treatment.^[7]^ It has been proved that there possibly exists a brain–gut interaction in the treatment of insomnia. However, due to various limitations in the clinical diagnosis, treatment standards, and medical ethics, there is still a lack of research on the specific mechanism of brain–intestinal interaction in the treatment of insomnia by abdominal massage.

Hypothalamus-pituitary-adrenal gland (HPA) is an important mechanism for coordinating the nervous system and endocrine system. It participates in the stress response of the nerve center, and also controls the regulation of gastrointestinal smooth muscle contraction and mucosal transport.^[8]^ The changes in the gastrointestinal motility, mucosal secretion, and intestinal permeability will have a significant impact on the microbiota in the gastrointestinal tract. HPA axis system consisting of the hypothalamus paraventricular nucleus of the hypothalamus (PVN) is one of the important regulating center brain–gut interaction mechanism. The hypothalamus paraventricular nucleus can secrete adrenal cortical hormone releasing hormone (CRH),^[9]^ that can stimulate the activation of HPA activation, CRH can then bind to corticotropin releasing hormone type I receptor (CRHR1) through its receptor binding reaction, thereby promoting the pituitary to secrete adrenocorticotropic hormone (ACTH). This hormone then circulates throughout the body and can stimulate the adrenal glands, leading to the secretion of cortisol (CRO) from the adrenal cortex. CRO has been reported to be an important medium between HPA axis and the human body endocrine and closely associated with sleep. CRO is a glucocorticoid, which is widely used clinically as an effective anti-inflammatory and immunosuppressive agent.^[8]^ Moreover, a number of reports have found that sleeping <5 hours in cases may be associated with CRO,^[10]^ as in the beginning of sleep HPA axis is restrained, and CRO secretion can be reduced transiently. However, generally in the middle of the night when CRO level reaches its lowest concentration, it can lead to a gradual increase in the activity of HPA axis after the start of the sleep and this increase has been reported to peak around 9 o ’clock in the morning.^[11]^ Thus, the concentration of CRO and ACTH can be effectively detected in the blood samples of insomniacs, and it has been found to be more obvious in the afternoon, evening, and early morning. Additionally, both ACTH and CRO could potentially serve as an important factor in research on insomnia and HPA axis, but the available research data of patients with insomnia and HPA axis, only involves the role of ACTH and CRO, but has limited information on the pathway upstream substances. As the initiating factor of the hypothalamus, CRH is a key substance of the HPA axis. It is a key substance that causes insomnia after the human body is exposed to stress. At present, relevant research on the HPA axis of insomnia patients should primarily focus on the role of various upstream substances regulating this pathway.

The proposed clinical trial will determine the possible effects of abdominal ring-rubbing method on sleep quality of insomnia patients by using neuropsychology, resting state brain functional MRI (RS-fMRI), and metabonomics, and will clarify the role of the brain–gut interaction mechanism of abdominal ring-rubbing method in improving the sleep quality.

## Methods and design

2

### Objectives

2.1

Study objectives: to determine the potential efficacy of treatment of insomnia ring vibrating abdominal kneading method. To decipher the various neural mechanisms underlying vibrating abdominal ring rubbing method for treating insomnia.

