### Statistical method

2.13

Spss23.0 statistical software will be used for statistical analysis for all the data generated. Chi-square test will be used for enumeration data, paired *t* test will be used for the comparison of measurement data before and after the treatment. One-way analysis of variance (ANOVA) will be used for comparison between the treatment groups, with *P* < .05 as difference and *P* < .01 as significant difference.

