Based on the theory of brain–gut interaction in the treatment of insomnia with abdominal massage, this study will further analyze the possible relationship between hypothalamus and brain–gut axis, CRH/CRHR1 pathway and sleep, and between HPA axis and sleep. On the basis of previous research and literature analysis, it has been established that the hypothalamus CRH/CRHR1 signaling pathway may play a pivotal role in the initiation of the HPA axis, coordination of the important pathways in the human nervous and endocrine systems but can also participate in the central nervous stress reaction, and can be involved in regulating the gastrointestinal smooth muscle contraction and mucous membrane of transshipment and thereby may play an important role in the process of brain gut interaction. Therefore, the proposed hypothesis that the treatment of insomnia by abdominal vibration and ring massage could be related to the intervention of hypothalamic CRH/CRHR1 signaling pathway, activation of HPA axis, regulation of different mediators such as ACTH, COR, 5-HT, GABA, and other metabolites in the body, thus contributing to the maintenance of neuroendocrine homeostatic state will be analyzed.

In this project, insomnia patients will be used as research objects, and scale screening, fMRI test, MRS test, serum ^1^HNMR test, and serum ELISA test will be carried out, so as to clarify the efficacy and influence on the HPA axis as a result of abdominal vibration and ring massage on insomnia patients from the clinical perspective.

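### The stated question is whether massage works, but the only randomised contrast is massage against a TCM bolus with no reported effect, so a non-significant difference cannot separate two effective treatments from two ineffective ones

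*Protocol article*

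**What the plan says.** - **Question.** The first objective in section 2.1 is "to determine the potential efficacy of treatment of insomnia ring vibrating abdominal kneading method". Section 3 (Discussion) repeats it: the tests are done "so as to clarify the efficacy and influence on the HPA axis as a result of abdominal vibration and ring massage on insomnia patients". Neither sentence names a comparator.
- **Arms.** The Abstract (Methods and design) states "Sixty insomnia volunteers will be randomly divided into a drug group and a massage group". The third group is not part of that randomisation: "30 healthy volunteers will be assigned to the healthy group". No placebo, sham, waiting-list or untreated patient group is described.
- **Comparator.** "Patients in the drug group will be given orally spleen-invigorating bolus" (Abstract). The support given is that "the drug group uses the recommended drug in the TCM guidelines", which the article places in its limitations sentence. On the wider class, which takes in TCM along with other non-conventional treatments, section 1 reports that they "are still not recommended in European Guideline for Diagnosis and Treatment of insomnia due to the poor quality of medical evidences".
- **Analysis.** Section 2.13 uses paired t tests for change within groups, and "One-way analysis of variance (ANOVA) will be used for comparison between the treatment groups", at P < .05. It states no non-inferiority or equivalence hypothesis.
- **Size.** Section 2.2 gives a calculated n of 16.76 per group and plans 30 per group. It states no effect size, SD, power or reference treatment.

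**The concern.** A two-arm comparison with an active treatment estimates massage minus bolus. It answers whether massage works only if massage wins, or if the effect of the bolus is known from elsewhere. The article supplies no such effect, so the stated question and the randomised contrast do not match.

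The gap matters most for a plausible outcome: both arms improve from baseline and the between-arm test is not significant. With a general efficacy objective and before-after tests in the plan, that result is open to being reported as massage working, or as massage equalling a recommended drug. Neither conclusion would follow. The healthy volunteers do not help. They have no insomnia and are not randomised, so they do not show what would happen to untreated patients.

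**Working it through.** **1. The plan's own figure.** n = 16.76 cannot be reproduced, because section 2.2 gives no inputs. Solving backwards with d = sqrt(2(z_alpha + z_beta)² / n), two-sided alpha 0.05 and 80% power:

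d = sqrt(2 × (1.960 + 0.842)² / 16.76) = 0.97 SD (1.00 SD with the t distribution).

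Other readings of the same n give 1.12 (90% power), 0.86 (one-sided, 80%) or 0.68 (paired, two-sided, 80%). The size therefore does not show which contrast was meant.

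**2. Precision of the randomised contrast.** Inputs: 30 per arm (section 2.2) and SD = 1 as the unit.

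- 95% interval half-width = t(0.975, 58) × sqrt(2/30) = 2.002 × 0.258 = 0.517 SD.
- Power for a true difference of 0.5 SD (two-sided t test) = 0.478.

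A non-significant result therefore leaves room for moderate differences in either direction.

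**3. Can the planned tests separate the two explanations?** 40,000 trials were simulated per scenario, with 30 per arm and change scores with SD 1. The mean changes are assumptions. The outcome counted is both paired tests significant and the between-arm test not significant.

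| Mean change in both arms | Source of the change | Frequency |
|---|---|---|
| 0.8 SD | all treatment effect | 93.7% |
| 0.8 SD | all non-specific | 93.5% |
| 0.5 SD | 0.3 treatment + 0.2 non-specific | 56.3% |
| 0.5 SD | all non-specific | 56.3% |

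The small gap in the first pair is simulation error, since the data have the same distribution in both rows. Non-specific change is to be expected: section 2.6.1 requires PSQI above 7 at entry, so some fall will occur through regression to the mean alone. The paired tests have no untreated reference with which to remove it.

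**4. Illustration only: dilution by an active bolus.** Assume massage gives 1.0 SD over no treatment, and let the bolus give a share of that. Power at 30 per arm (two-sided t test):

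| Assumed bolus share | Difference (SD) | Power |
|---|---|---|
| 0% | 1.00 | 0.968 |
| 25% | 0.75 | 0.815 |
| 50% | 0.50 | 0.478 |
| 75% | 0.25 | 0.159 |

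Both the 1.0 SD and the shares are assumptions. The article states neither.

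**5. Which groups enter the ANOVA.** The Abstract compares massage with both the healthy and the drug group, so the ANOVA may have three groups. An omnibus F could then be significant simply because insomnia patients differ from healthy volunteers, which says nothing about massage.

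**6. Whether the drug arm exists.** The Abstract has 60 patients in two randomised arms. Section 2.2 recruits 30 patients and 30 healthy volunteers, section 2.3 says participants receive massage, and section 2.10 describes massage for 30 patients and no drug regimen. If those sections governed, there would be no randomised comparator at all.

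**The case against.** An active comparator recommended in a guideline is a legitimate choice, and a significant result favouring massage would be informative. The objective is hedged by the word potential, and short general objectives are normal in an article. No equivalence or non-inferiority claim is planned, so the misreading is only a risk. The article already lists the comparator among its limitations. All of this stands, but the limitations sentence does not say what the comparator choice means for inference.

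A reader might infer that the article itself calls the bolus unsubstantiated. It does not. Section 1 reports a European guideline's position on a broad class that could equally cover the massage, and it says nothing specific about this product.

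A reader might also infer that the effect of the bolus is unknown. The document shows only that no effect is reported here. Evidence may sit in the full protocol or in the TCM guideline.

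It can be said, too, that a full analysis plan might add a non-inferiority margin. At 30 per arm (one-sided 0.025, 80% power, no true difference) the margin would have to be about (1.960 + 0.842) × sqrt(2/30) = 0.72 SD. Non-inferiority would still not show efficacy without evidence that the bolus works.

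**Conclusion.** The point holds as a mismatch between the stated objective and the randomised contrast. As written, the plan can support superiority of massage over the bolus. It cannot support efficacy of massage from a non-significant between-arm result, whatever the before-after tests show. The half-width of 0.52 SD depends only on 30 per arm and a two-group comparison in SD units. The simulated frequencies rest on assumed mean changes, but the inability to separate the two explanations does not.

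The power series is an illustration and should not be read as the trial's power. The tempting stronger reading, that the trial can say nothing about efficacy, is not supported: a clear win for massage would be evidence, subject to the unclear single blinding. All of this presumes the two-arm design of the Abstract, which the Methods sections contradict.

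**What to change.** 1. Reconcile sections 2.2, 2.3 and 2.10 (30 patients, massage only) with the Abstract (60 patients, two randomised arms). The other steps assume that a randomised drug arm is confirmed.
2. Reword section 2.1 and the matching sentence in section 3 as comparative: whether abdominal massage improves sleep quality more than the spleen-invigorating bolus.
3. In section 2.13, make the randomised massage-minus-drug difference with its 95% confidence interval the efficacy result. Use one named sleep scale already collected, for example PSQI, at end of treatment and at the 4-week follow-up. This replaces before-after tests, or an omnibus ANOVA that may include the healthy group, as the basis for efficacy. The article names no primary outcome, so the choice of scale is the sponsor's.
4. State in advance that a non-significant difference will not be read as equal effectiveness or as evidence that massage works.

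Steps 2 to 4 change wording and analysis only and need no further patients or measurements. The downside is a narrower claim. A claim of absolute efficacy would need either an untreated, sham or placebo reference or documented evidence of the comparator's effect.

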### Setting

2.2

The patients will be recruited from the Department of Zang-fu Massage, Affiliated Hospital of Changchun University of Chinese Medicine. Additionally, for participating in the trial, the patients will be screened strictly according to the diagnostic criteria, inclusion criteria, and exclusion criteria, and the requirements for the sample size estimation will be based on the clinical calculation formula employed for small sample size. The sample size (n = 16.76) will be calculated, that is, the therapeutic effect could be judged by the sample size of >16.67 people in each group. In this study, therefore 30 people will be observed in each group, which met the sample size estimation criteria.

The trial researcher will be able to record the subject's basic information (such as date of birth, sex) and answer patient trial screening questions. After the various patients have completed screening and enrolled, the trial study serial number, that is, the patient's unique identification number (SIN), will be obtained according to the enrollment time and order of enrollment, until the total number of observations (30 cases) was completed. Thirty healthy volunteers and 30 patients will be recruited for the study. After clinical evaluation and blood sampling, abdominal massage therapy will be adopted.

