### Participants and recruitment

2.3

The recruitment posters will be displayed in the hospitals and forward recruitment information will be posted on WeChat to recruit the potential participants for this study. The participants will be explained in detail about the potential benefits and services to be provided and the risks associated with participating in the study, including adverse clinical outcomes that may be associated with abdominal massage therapy. A detailed reading and an informed consent will be signed by each participant prior to the participation. On the consent form, participants will also be asked whether they provide consent to use their data even if they opt out of the trial. The participants will also be required to obtain permission for the research team to share relevant information with staff from the participating hospitals or regulatory agencies. The participants will receive 4 different courses of abdominal massage therapy. In addition, 30 healthy age- and sex-matched, volunteers with good sleep pattern will be recruited as the healthy controls. The personal information of all the participants will be kept confidential by the researchers and used only for this study.

The patients must properly understand and sign informed consent. Pittsburgh Sleep Index scale (PSQI), Hyperarousal scale (HAS), Hamilton Depression Scale (HAMD), and HAMA scores will be used to potentially determine whether participants meet the inclusion criteria. Patients who met the criteria will thereafter be included in the study (Fig. 1).

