### Treatment programs

2.10

After being enrolled, 30 patients will be treated with abdominal vibration and ring kneading therapy. The main techniques that will be used include rubbing the abdomen, shaking the abdomen, and pressing the abdomen. The main points to be considered will be Zhongwan (CV12), Shenque (CV8), Zhongji (CV3). The acupoint location that will be used refers to the 2006 National Standard of the People's Republic of China (GB/T12346-2006) “Acupoint Name and Location.”

During the treatment, room temperature will be kept appropriate, and the environment quiet and tidy. The patient will be laid in the supine position, exposing the abdomen and maintain it in a relaxed state. The doctor will sit on the right side of the patient. The doctor will rub the entire abdomen clockwise with CV 8 as the center for 5 minutes, up to CV 12, and down to CV 3. The left and right sides will be placed between the left and right meridians of the foot Taiyin Spleen meridian, so as to regulate the air movement and allow the blood to flow. Thereafter, the whole abdomen will be kneaded with both hands for 10 minutes to adjust the internal organs and to balance the yin and yang. CV 12 will be vibrated with one hand for 2 minutes, palm CV 8 for 3 minutes, and flash CV 3 for 5 minutes with one hand, at a frequency of >200 times per minute to invigorate the spleen and stomach, and replenish qi and blood. Thereafter, abdomen will be pressed with the palm of the hand centered on CV 8, it will be pressed deeply while breathing in, and will be lifted gently while breathing out, for 5 minutes, to induce the air to return to the original body, and to calm the mind. Patients will undergo the therapy for 30 minutes duration each time, once a day, 5 days as a course of treatment, the treatment interval will be 2 days, and intervention will be conducted over 4 courses. There will be a follow up conducted once during the 4th week after the treatment.

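### The abstract randomises 60 patients to massage or drug, but the legible Methods recruit 30 patients and define only massage; patient number, arms and allocation must be reconciled

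*Protocol article*

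**What the plan says.** The abstract (Methods and design) gives the numbers and the allocation: "Sixty chronic insomnia volunteers and 30 healthy volunteers will be recruited for this study", and "Sixty insomnia volunteers will be randomly divided into a drug group and a massage group". It also gives the comparator: "Patients in the drug group will be given orally spleen-invigorating bolus, twice a day". The advantages and limitations text after the abstract mentions the comparator again: "the drug group uses the recommended drug in the TCM guidelines". The same text also describes the trial as performing only massage in patients.

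The Methods read differently:

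- Section 2.2 says that the patient's serial number "will be obtained according to the enrollment time and order of enrollment, until the total number of observations (30 cases) was completed". It then states: "Thirty healthy volunteers and 30 patients will be recruited for the study. After clinical evaluation and blood sampling, abdominal massage therapy will be adopted".
- Section 2.3, without separating any arms: "The participants will receive 4 different courses of abdominal massage therapy".
- Section 2.10: "After being enrolled, 30 patients will be treated with abdominal vibration and ring kneading therapy". No other treatment is described under that heading.
- Section 2.11.4 draws blood from the healthy group and one patient group.
- Section 2.13 plans a paired t test for change over treatment and a one-way ANOVA between treatment groups.

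**The concern.** The two accounts give different patient numbers, different numbers of groups and a different basis for comparison. The concern is not that a condensed article leaves out how randomisation is done. It is that section 2.2 states a recruitment total and an enrolment stop that conflict with the total in the abstract.

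The consequence is what the trial can conclude. Section 2.1 sets efficacy as an objective. Without a randomised comparator, two contrasts remain. The first is before against after in massaged patients. It mixes any treatment effect with natural course, expectation and regression to the mean, and regression is a live issue because section 2.6.1 admits patients on a PSQI above 7. The second is patients against healthy volunteers, who were selected for not having insomnia, so it says nothing about what the patients would have scored without massage.

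**Working it through.** **Head count**

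| Item | Abstract | Methods, legible text |
|---|---|---|
| Patients recruited | 60 | 30 (2.2) |
| Healthy volunteers | 30 | 30 (2.2) |
| Total | 60 + 30 = 90 | 30 + 30 = 60 |
| Groups of 30 | 90 / 30 = 3 | 60 / 30 = 2 |
| Treatments defined for patients | massage, drug | massage (2.2, 2.3, 2.10) |
| Random allocation | stated | not stated |
| Patient groups giving blood | not specified beyond three study groups | one (2.11.4) |

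The difference is 60 − 30 = 30 patients, exactly the size of the drug arm under an equal split.

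**Does the sample-size statement settle which design is meant?** Section 2.2 gives n = 16.76 (then 16.67) per group and rounds up to 30 per group. The figure cannot be reproduced, because no effect size, standard deviation, power or sidedness is given. Inverting the usual normal-approximation formulas shows what it would imply:

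- two groups: n = 2(z_α + z_β)² / d², so d = √(2(z_α + z_β)² / 16.76)
- paired: n = (z_α + z_β)² / d², so d = √((z_α + z_β)² / 16.76)

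For example, with two-sided alpha 0.05 and 80% power (assumed), z_α + z_β = 1.960 + 0.842 = 2.802. Then d = √(2 × 7.85 / 16.76) = 0.97 for two groups, and √(7.85 / 16.76) = 0.68 for paired data. Over one- or two-sided tests, alpha 0.05 or 0.01, and power 80% or 90% (all assumed), the range is 0.86 to 1.33 for two groups and 0.61 to 0.94 for paired data. The figure therefore does not show whether a between-arm or a before-after comparison was sized. Thirty per group fits 2 × 30 as well as 3 × 30.

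**What each account yields if followed**

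- Methods as written: 30 massaged patients and 0 randomised controls. The paired t test is uncontrolled. With two groups, the one-way ANOVA reduces to a two-sample t test of patients against healthy volunteers.
- Abstract's allocation combined with the stop at 30 cases in section 2.2: 30 / 60 = half of the patients. Split equally (assumed), that is 30 / 2 = 15 per arm, below the article's own 16.76.

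**The case against.** The strongest reply is that this is a three-group trial, incompletely written up. Several places fit that reading. The limitations text names the drug group. Section 2.2 speaks of 30 people in each group, and section 2.11.1 assesses patients in each group. Section 2.8 refers to a random medical record number. Section 2.13 compares treatment groups in the plural. Section 2.10 taken alone fits the 30-patient massage arm of a 60-patient trial. The stop at 30 cases might have been meant per group.

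Much of this stands, and it limits the claim in four ways:

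- A reader might infer that the study is really single-arm. The evidence is mixed and does not establish that.
- A reader might infer that every patient is assigned massage. The article never says so; this is only the combined sense of sections 2.2, 2.3 and 2.10.
- A reader might infer that the protocol contains no drug arm or allocation step anywhere. Figure 1, the flow chart, is not available to this review and may show both, so the statement covers the legible Methods text only.
- A reader might take section 2.3 as what participants are told. It is protocol text, and the consent form was not available.

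The reply does not remove the conflict. None of these phrases defines a second patient arm. Section 2.2 calls 30 the total number of observations and gives 30 patients as the number recruited. A flow chart with a drug arm would contradict section 2.2, not cure it. Condensing a protocol can drop detail, but it does not change 60 patients to 30.

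**Conclusion.** The point holds as an internal contradiction on patient number, arms and allocation. Patient numbers differ by a factor of two (60 against 30), total numbers are 90 against 60, and the shortfall of 30 equals one whole arm. Under the Methods as written there is no randomised comparator, and the efficacy objective in section 2.1 cannot be supported.

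This rests on the legible text alone. It assumes nothing about which account was approved, and the document does not settle that. It must be resolved before the trial is run or reported, because the presence or absence of a randomised comparator decides what the results can mean.

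**What to change.** Reconcile the abstract, the advantages and limitations text, and sections 2.2, 2.3, 2.10 and 2.11.4 on the number of patients, the arms and the allocation.

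*If the randomised trial is what was approved:*
- in 2.2, state 60 patients with insomnia (30 massage, 30 drug) and 30 healthy volunteers, and set the patient recruitment total at 60;
- keep the enrolment-order serial number as an identifier only, and say that it is not used for allocation;
- in 2.3, limit the massage sentence to patients randomised to massage;
- in 2.10, name the drug arm, and in 2.11.4 name each group that gives blood.

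*If only 30 patients will be enrolled:* remove the randomised controlled label, and limit conclusions to before-after change and a non-randomised comparison with healthy volunteers.

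The cost depends on which account is true. If 60 was approved, this is a wording correction with no added patients. If 30 was the working number, moving to the randomised design adds 30 patients, doubling patient recruitment. Section 3.1 dates ethics approval to April 2021 and expects recruitment to be complete by June 2022, so that change may need an amendment.
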